**Study goals and objectives**

The primary aim of this study is to evaluate the effects of aerobic–resistance versus resistance–aerobic exercise sequences within concurrent training on cardiovascular function and biochemical biomarkers in patients with Type 2 diabetes, based on the evidence gaps identified in a prior systematic review and meta-analysis.

**Study design**

This study adopts a two-phase sequential research design to investigate the impact of exercise sequence in concurrent training on patients with type II diabetes. Phase I involved conducting a systematic review and meta-analysis titled “Effect of concurrent continuous aerobic and short rest resistance exercise training on metabolic biomarkers in type 2 diabetes patients: a systematic review and meta-analysis.” This review aimed to summarize and synthesize existing evidence on the effects of concurrent training on metabolic outcomes such as HbA1c, insulin resistance, and lipid profile. The review identified both clinical and methodological gaps in the current literature, with a notable lack of evidence on the role of exercise sequence: specifically, whether performing aerobic training before or after resistance training and controlling confounding variable has differential effects on key metabolic and cardiovascular biomarkers in this population.

Building on the findings from the systematic review, Phase II employs a parallel-group randomized controlled trial (RCT) to address the gaps identified. The trial focuses on the sequence of exercise as a potentially important but under-researched variable in concurrent training programs for individuals with type II diabetes. Participants will be randomly allocated in equal numbers to one of three groups: the CART group (Concurrent Aerobic then Resistance Training), the CRAT group (Concurrent Resistance then Aerobic Training), and a wait-list control group (COT). Randomization will follow a 1:1:1 ratio and will be stratified by sex and age, with participants grouped into four age categories: 41–45 years, 46–50 years, 51–55 years, and 56–60 years. To reduce allocation bias, the randomization process will be overseen by the personal trainer and the principal researcher, while outcome assessments will be conducted by independent data collectors blinded to group assignment.

The intervention will last for 12 weeks, with participants in the CART and CRAT groups engaging in supervised concurrent training sessions for one hour per day at 5:00 PM on Tuesdays, Thursdays, and Sundays. Although the types of exercises will be identical between the two intervention groups, the order of aerobic and resistance training will differ. The researcher will monitor and compare changes in anthropometric measures, cardiovascular function, and biochemical biomarkers across the groups through pre- and post-intervention assessments. This two-phase design ensures that the RCT is grounded in a comprehensive evidence base and targets specific unanswered questions identified in the literature, thereby enhancing both the scientific rigor and practical relevance of the study.

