**Research protocol: part 1**

**Project summary**

Type II diabetes mellitus (T2DM) is a progressive metabolic disorder associated with impaired glycemic control, insulin resistance, and elevated cardiovascular risk. Exercise is a well-established non-pharmacological therapy; however, the optimal sequencing of aerobic and resistance training in concurrent exercise programs remains unclear. Clarifying whether exercise order influences cardiometabolic adaptations is essential for refining exercise prescriptions in T2DM management.

The objective of this randomized controlled trial is to investigate the effect of exercise sequence on cardiovascular function and biochemical biomarkers in patients with T2DM. Specifically, the study compares the effects of aerobic–resistance versus resistance–aerobic training sequences on insulin resistance, glycemic control, lipid profile, and cardiovascular function.

A total of 39 men and women aged 41–60 years are recruited and randomly allocated into three groups: concurrent aerobic–resistance training (CART), concurrent resistance–aerobic training (CRAT), and a non-exercising control group (COT). Allocation is stratified by age and sex. The intervention spans 12 weeks, with supervised exercise sessions conducted three times per week. In CART, aerobic exercise precedes resistance training, whereas in CRAT, resistance exercise precedes aerobic training. The control group maintains standard care without structured exercise.

The primary outcomes include changes in cardiovascular function and biochemical biomarkers response. Secondary outcomes include anthropometric indices (BMI, body fat percentage, and waist–hip ratio).

This trial is expected to demonstrate that concurrent training improves metabolic and cardiovascular health in T2DM patients, with potential sequence-specific effects. Findings provide practical evidence for optimizing exercise prescriptions and enhancing the clinical management of T2DM

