**Data management and statistical analysis**

All data will be systematically coded and entered into a secure, password-protected database for computer-assisted analysis. Data handling procedures include double-entry verification and regular monitoring to ensure accuracy, completeness, and consistency. Any discrepancies or spurious entries will be flagged and resolved through cross-checking with source documents.

Statistical analysis will be performed using SPSS version 27. The primary analytical approach is Repeated Measures Analysis of Covariance (RM ANCOVA), which allows for the evaluation of time-dependent changes across intervention groups while controlling for dietary practice as a covariate. This adjustment accounts for individual variability in nutritional habits that may influence metabolic outcomes.

The model will assess:

- **Main effects of time** (pre- vs post-intervention),
- **Main effects of group** (CART, CRAT, COT),

Assumptions of normality, homogeneity of variance, and sphericity will be tested prior to analysis. Violations will be corrected using appropriate statistical adjustments (e.g., Greenhouse-Geisser correction). The level of significance is set at *p* < 0.05, and partial eta squared (η²) will be reported to indicate effect sizes.

The sample size of 39 was determined through power analysis, targeting 80% power to detect moderate effect sizes in insulin resistance and cardiovascular outcomes, with a 5% significance level and allowance for 10% attrition.

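### The primary model uses baseline only as a repeated outcome and omits sex and age, the stratification factors, so a 39-person trial gives up precision it could recover at negligible cost

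*Protocol*

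**What the plan says.** **Allocation** (Protocol, Study design). On arm sizes the section states: "Participants will be randomly allocated in equal numbers to one of three groups". The ratio is 1:1:1, and allocation is to be "stratified by sex and age, with participants grouped into four age categories: 41–45 years, 46–50 years, 51–55 years, and 56–60 years". Both sexes are enrolled according to the Project summary: "A total of 39 men and women aged 41–60 years are recruited". That makes 2 × 4 = 8 strata.

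**Analysis** (Protocol, Data management and statistical analysis). The primary approach is a repeated-measures ANCOVA run "while controlling for dietary practice as a covariate". The effects listed are time (pre against post) and group. Sex, age and age band are not mentioned, and the baseline value appears only as the pre-intervention level of time.

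**Sample size** (same section). The basis given is this: "The sample size of 39 was determined through power analysis". Its aim is described as "targeting 80% power to detect moderate effect sizes in insulin resistance and cardiovascular outcomes". The test level is 5% and the attrition allowance 10%. No numerical effect size, SD or pre-post correlation is given.

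**The concern.** The Protocol constrains allocation on two factors and then leaves both out of the model it names as primary. It also measures every outcome at baseline, but uses that measurement as a second response rather than as a predictor of the week-12 value. With 13 people per arm, and the comparison of the two exercise sequences as the primary aim, there is little power to spare. Baseline, sex and age are already collected, so using them needs no extra participants or visits.

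At stake is the width of the interval for CART against CRAT, and so the chance of detecting a sequence effect if there is one.

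**Working it through.** **1. The stated sample size.** The figure of 39 cannot be confirmed from the stated inputs. For the group-by-time test with three arms and two time points, the noncentrality is λ = f² × N × 2/(1−r), with 2 and N−3 degrees of freedom. Taking moderate as f = 0.25 and r = 0.6 (both assumed) gives 35 completers, and 35/0.9 = 38.9, so 39. With the same f, r = 0.5 needs 42 completers (47 with attrition) and r = 0.3 needs 58 (65). So 39 is attainable, but only under an unstated correlation. The range for r is therefore shown throughout.

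**2. Baseline as a repeated response against baseline as a covariate.** With two time points, the group-by-time test is the comparison of arms on change. For equal SD σ at both times and within-arm correlation r:

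- variance of change: 2σ²(1−r)
- residual variance of the week-12 value given baseline: σ²(1−r²)
- ratio: 2(1−r)/(1−r²) = 2/(1+r)

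Power below is for an assumed difference of 0.8σ between CART and CRAT, 13 per arm, two-sided 5%. The standard error is √(variance × 2/13). At r = 0.5 it is √(1.00 × 2/13) = 0.392σ for change and √(0.75 × 2/13) = 0.340σ for ANCOVA.

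| r (assumed) | Variance ratio | 39 × ratio | Power, change | Power, ANCOVA |
|---|---|---|---|---|
| 0.3 | 1.54 | 60 | 39% | 55% |
| 0.5 | 1.33 | 52 | 51% | 63% |
| 0.7 | 1.18 | 46 | 73% | 79% |
| 0.8 | 1.11 | 43 | 88% | 91% |

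The third column is the number a change analysis would need to match ANCOVA on 39. In terms of the difference detectable with 80% power, ANCOVA lowers it from 1.13 to 0.98 SD at r = 0.5 and from 0.88 to 0.81 SD at r = 0.7.

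**3. Leaving out sex and age.** Simulations of 39 people in 8 strata, with assumed permuted blocks of three and r = 0.6, looked at the change model without strata:

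- Strata unrelated to outcome: type I error 0.049, 95% interval width 1.413. Adding seven stratum dummies widens it to 1.448, about 2.5%.
- Strata that shift pre and post equally: type I error 0.049. The differencing already removes the effect.
- Strata that explain 10%, 20% or 40% of the variance of change: type I error 0.044, 0.034 and 0.014. At 20%, the model's standard error is 0.395 against a true 0.362.

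So omission matters only if sex or age predicts change, and then the analysis is conservative.

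**4. How to enter them.** Beside baseline, sex plus linear age gave an interval width of 1.296, against 1.323 for seven dummies, when strata explained 10% of the variance of change. With unrelated strata the widths were 1.294 and 1.323. The comparison favours the linear term to the extent that the real age effect is close to linear.

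**5. Degrees of freedom.** 39 − 3 arms − 1 diet = 35. Taking off baseline, sex and age leaves 32. The 97.5% t quantile goes from 2.030 to 2.037, or 0.3%. ANCOVA power at r = 0.5 is 62.9% on 35 and 62.7% on 32.

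**6. Equal numbers.** With assumed blocks of three and equally likely strata, exactly 13/13/13 arises in about 15% of randomisations, and a gap of three or more between arms in about a third. The cost is small. Relative to 13 v 13, the contrast variance rises by (1/12 + 1/14)/(2/13) − 1 = 0.6% for 12 v 14, and by (1/11 + 1/14)/(2/13) − 1 = 5.5% for 11 v 14.

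**The case against.** A reader might infer from the omitted factors that the trial's error bars are wrong. The documents do not support that. Using baseline as a response rather than a covariate loses precision but leaves the standard error valid. Omitting sex and age distorts it only if they predict change, which no figure in the Protocol shows, and the distortion then makes intervals too wide. No excess of false positives follows.

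A reader might also conclude that the strata should be redrawn. That does not stand. The Protocol Identifying Number section says registration was completed during the intervention, so allocation had already happened. Four strata with blocks of three would give exact balance in only about 29% of randomisations, and imbalance of the size expected here costs little.

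Adjustment is not free in every form: seven stratum dummies would slightly widen the interval if the strata were not prognostic. Nor is there a case for dropping diet, since controlling for it is part of the trial's stated rationale.

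Finally, the Project management section gives the statistician an analysis plan, which is not shown and could add covariates. That has some force for sex and age. It is weaker for baseline, because the Protocol itself names the primary model and sets baseline as a level of time. The same section describes that plan as including the RM ANCOVA modelling.

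**Conclusion.** The point holds as a loss of efficiency in a model the Protocol has fixed. Treating baseline as a response inflates the variance of the arm comparison by 11% to 54% for r from 0.8 down to 0.3. It costs 3 to 16 percentage points of power for a 0.8 SD difference. The loss exists at every r below 1 and is smallest when r is high.

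The size rests on assumed values of r, an assumed difference of 0.8 SD, equal variances at the two times and 13 completers per arm. It also reads the repeated-measures model as comparing change between arms. The gain from sex and age is conditional and cannot be sized from the Protocol.

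The Rationale section speaks of middle-aged men, against men and women in the Project summary. If only men were enrolled, there would be four strata and no sex term. The two statements need reconciling.

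**What to change.** In Data management and statistical analysis, state the primary model for each outcome as: week-12 value = arm + baseline value + sex + age in years (continuous) + the dietary covariate already planned. Enter sex and continuous age rather than seven stratum dummies.

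In Study design, change the promise of equal numbers to approximately equal numbers. Leave the stratification as it is.

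The cost is an amendment to the wording and about three error degrees of freedom (35 to 32). No new data are needed. Because the trial is under way, date the change and make it before outcome data are examined by arm.

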**Methodology**

**Method and Procedures of Data Collection**

The data collection for this study will be conducted under carefully controlled environmental and procedural conditions to ensure consistency and accuracy of results. Every subject will be assessed for the same variables at the same time of day to minimize variations, which can significantly influence physiological responses such as cardiovascular function and biochemical biomarkers. The experimental room will maintain a relatively constant air humidity and temperature to prevent external factors, such as fluctuating environmental conditions, from affecting the participants' responses. This consistency in timing and environment is crucial for reducing potential variability in the data and ensuring that any observed effects can be attributed to the exercise interventions rather than external factors.

Additionally, all research and laboratory staff involved in the data collection will be rigorously trained and instructed to adhere to specific protocols to avoid influencing the participants during the assessments. They will be required to remain still and silent throughout the procedures, reducing any potential distractions or stressors for the participants.

**Measurement of biochemical variables**

Blood samples will be drawn from the antecubital vein both before and after the 12-week exercise training period. 48 hours after the most recent training session, blood samples will be taken to minimize the acute effects of exercise and ensure accurate results. In addition, participants must refrain from eating or drinking alcohol and coffee for 12 hours before the blood sample test, as well as avoid consuming alcohol or eating a high-fat diet.

The blood samples will be collected by a medical laboratory technician from Debre Markos Referral Hospital, who was trained in the procedure. A trained technician will utilize a venipuncture to extract blood from the antecubital vein while the participants will be seated. These samples will then be analyzed to evaluate various biochemical parameters. With some careful planning and preparation, a single blood draw will be used to acquire the sample to evaluate all of the biomarkers (HbA1c, Insulin Sensitivity, Glucose Tolerance, HDL, LDL, TC and Triglycerides) based on preplanned standard operating procedures.

**Blood collection tools**

- Blood collection tubes (e.g., EDTA, serum separator tubes).
- Sterile needles and syringes
- Alcohol swabs
- Tourniquet
- Cotton balls
- Sharps disposal container

**Venipuncture Procedure**

Position the patient comfortably in a seated position, with the arm fully extended and the palm facing upward. Select an accessible vein, typically in the antecubital fossa, while avoiding areas with bruises, scars, or inflammation. Apply a tourniquet 3–4 inches above the venipuncture site and check for an easily accessible vein. Clean the site thoroughly using an alcohol swab in a circular motion, starting from the center and moving outward, and allow it to air dry completely. Press the vein by holding the skin with your thumb below the puncture site, and insert the needle bevel side up at a 15–30-degree angle.

For sample collection, follow the correct order of draw to avoid cross-contamination by collecting blood in a serum separating tube (SST) for the fasting insulin, lipid profile. Ensure sufficient blood volume is collected for all tests, typically 5 mL per tube for serum tests and 2–3 mL for HbA1c. Invert the tubes as needed for proper additive mixing, and label each tube immediately with the patient’s name, date of birth, date, and time of collection.

Since Debre Markos lacks a facility for fasting insulin level tests, the blood samples will be securely transported to the Wudassie Diagnostic Center in Addis Ababa for analysis. After collection, the fasting insulin sample will be placed in a serum separator tube (SST) and immediately labeled with the patient's information, date of birth, and time of collection. The sample will be stored in a cool, insulated container with an ice pack to maintain its integrity during transport. The sample should be delivered promptly to the diagnostic center to ensure accurate results, ideally within 24 hours. Upon arrival at the laboratory, the sample will be processed according to standard procedures for insulin level testing.

The Enzyme- Linked Immunosorbent Assay (ELISA) assay type China (Shakil-Ur-Rehman et al., 2017) will be used for the fasting insulin test assays.

The homeostasis model of insulin resistance (HOMA-IR index), which is the product of glucose and insulin concentrations divided by a factor, will be used to quantify insulin resistance (Vogeser et al., 2007). The HOMA-IR index will be calculated as:

$$HOMA-IR=\frac{fasting serum glucose (mg.\mathrm{dL}^{-1})*fasting serum insulin(\mu U.{mL}^{-1})}{405}$$

*Equation 4* *Homeostasis model of insulin resistance equation*

**Measurement of cardiovascular function variables**

**Blood pressure**

The procedure for accurately measuring blood pressure and arterial stiffness using via an automated Sphygmocor XCEL device (AtCor Medical, CardieX, Sydney, Australia) (De la Torre Hernández et al., 2021), was adapted from Mengistu et al. (2025).

**Materials Required**

- SphygmoCor XCEL device
- The appropriate brachial cuff will be selected based on arm circumference: dark blue for 22-33 cm, maroon for 31-40 cm, and brown for 38-50 cm.
- A stable and flat table and comfortable bench.

**Preparation**

- **Participant Preparation:**
  - Instruct the participant to avoid caffeine, alcohol, and strenuous exercise for at least 30 minutes prior to measurement.
  - Make sure the participant has been positioned ready and lying on the catheterization laboratory table for at least 5 minutes before starting the procedure.
  - Ask the participant to remove any clothing that may obstruct the placement of the cuff on the upper arm.

**Procedure**

- **Cuff Placement:**
  - Place the cuff on the participant’s left upper arm, positioning it so that the artery marker aligns with the brachial artery.
  - Ensure the cuff is snug but not excessively tight, and the lower edge is approximately 2-3 cm above the elbow crease.
- **Positioning:**
  - Position the arm with the cuff at heart level for accurate readings. Use cushioning if needed to maintain proper positioning.
- **Initiating the Measurement:**
  - Begin the measurement by activating the SphygmoCor XCEL system.
  - The device will automatically record the brachial blood pressure (SBP and DBP) during cuff inflation and deflation.
- **Instructions During Measurement:**
  - Instruct the participant to remain still and refrain from speaking or moving during the cuff inflation and waveform measurement phases.
- **Post-Measurement**
- Remove the cuff and assist the participant to sit up if needed.
- Record the measurements displayed by the device:
  - Brachial SBP and DBP
  - Resting heart rate
- Conduct the measurement three times to ensure accuracy, adhering to standard protocols, and use the average of the remaining two readings.

**Covariate variable (dietary assessment)**

While nutrition is not a primary focus of the study, it should be monitored due to its potential impact on the dependent variable. Therefore, we will track the average daily calorie intake through face-to-face interviews. We will be utilized a 24-hour interactive personal interview with multiple passes (Quick list, Forgotten foods, Time & occasion, Detail cycle and Final probe) that was developed and validated for use in developing countries (Blanton et al., 2006; Gibson & Ferguson, 2008) (APPENDIX B). This approach employs five steps:

- Step 1: Quick list (a list is made of foods and drinks consumed in the last 24 hours)
- Step 2: Forgotten foods (questions are asked to identify any foods that may have been overlooked in Step 1)
- Step 3: Time & occasion (the time and occasion of each food item are recorded)
- Step 4: Detail cycle (each food's detailed description, quantity, and any additions are documented)
- Step 5: Final probe (a last check is done to ensure no other foods or drinks were consumed in the past 24 hours)

The 24-hour food frequency data collect on three non-consecutive two weekdays and one weekend days (Baranowski, 2012; Buttriss et al., 2017): from Monday 6 p.m. to Tuesday 5 p.m., Wednesday 6 p.m. to Thursday 5 p.m., and Saturday 6 p.m. to Sunday 5 p.m. It is better to choose non-consecutive days, as this helps to capture a broader range of variability in an individual's diet (FAO, 2018). We will apply the Ethiopian food composition table (EHNRI, 1981; EHNRI, 1998) to estimate nutrient and energy levels from dietary data. The names of foods and drinks, their descriptions, cooking methods, and amounts from 24-hour periods will be coded and submitted to the NutriSurvey200 (Feyesa et al., 2020). After determining the frequency of consumption per day, we will use the product sum approach to determine daily food intake. Daily food intake = ∑ (food item's stated consumption frequency, translate to times per day) * (portion size ingested of that food). The daily average energy intake will also determine as follows: ADEi = ∑daily food intake/number of data collected days.

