**Problems anticipated**

While the study is designed to be feasible within the proposed 12-week timeline and allocated budget, several challenges may arise during implementation. One key concern is participant retention, particularly in the intervention groups, due to time constraints, transportation issues, or health-related setbacks. To address this, flexible scheduling, regular follow-up calls, and motivational support will be provided to encourage adherence. Transportation stipends may be considered if budget permits.

Another potential difficulty is variability in dietary practices, which could confound metabolic outcomes. Although dietary practice is statistically controlled as a covariate, additional efforts will be made to monitor and reinforce consistent dietary behavior through brief nutritional guidance and regular check-ins.

Limited funding may restrict access to advanced diagnostic tools or biochemical assays. To mitigate this, cost-effective alternatives will be used where possible, and partnerships with local health institutions will be explored to access shared resources.

Data completeness and quality may also be affected by missing or inconsistent entries. This will be managed through rigorous data monitoring, double-entry verification, and early identification of discrepancies. Training sessions for data collectors and exercise supervisors will be conducted to ensure protocol fidelity.

These proactive measures aim to safeguard the integrity of the study and ensure successful delivery of outcomes within the stipulated timeframe and budget.

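### The only covariate in the primary model is dietary intake, apparently recorded during the intervention; if so, the adjusted contrast is not the total effect of the randomised regimen

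*Protocol*

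**What the plan says.** In Data management and statistical analysis, the Protocol makes repeated measures ANCOVA the primary approach, "while controlling for dietary practice as a covariate". No other covariate is named there.

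Covariate variable (dietary assessment) defines the measure: "we will track the average daily calorie intake through face-to-face interviews". It describes the recalls thus: "The 24-hour food frequency data collect on three non-consecutive two weekdays and one weekend days", and gives the windows as "from Monday 6 p.m. to Tuesday 5 p.m., Wednesday 6 p.m. to Thursday 5 p.m., and Saturday 6 p.m. to Sunday 5 p.m". The result is a single mean: "ADEi = ∑daily food intake/number of data collected days". The section does not say in which study week the recalls are taken, whether they come before or after allocation, or whether they are repeated.

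Study design schedules training "for one hour per day at 5:00 PM on Tuesdays, Thursdays, and Sundays". Problems anticipated adds, beyond the covariate adjustment, that staff will monitor and "reinforce consistent dietary behavior through brief nutritional guidance and regular check-ins".

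**The concern.** Adjusting a randomised comparison for a baseline variable is harmless and often helpful. Adjusting for a variable measured after allocation is different when treatment can change it. If training, or the order of its components, alters how much participants eat, part of the effect on glucose, insulin resistance or lipids may run through intake. Holding intake fixed removes or distorts that part, and randomisation no longer protects the comparison.

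The stated aim in Study goals and objectives is the effect of the two sequences on cardiovascular function and biomarkers, which is a total effect. A primary model that conditions on in-trial intake answers another question. If intake and outcome share causes that are not measured, the result need not be a clean direct effect either.

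**Working it through.** The Protocol gives no figure for the diet adjustment, so there is none to reproduce. The check has three parts.

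**1. Recall windows against sessions**

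- Each window runs from 6 p.m. to 5 p.m. the next day, which is 23 h. Three windows give 3 × 23 = 69 h, where three full days would be 72 h.
- The windows close on Tuesday, Thursday and Sunday at 5 p.m., which is the session start in Study design.
- With one-hour sessions ending at 6 p.m., the Monday and Wednesday windows open 24 h after the previous session ends and close 47 h after it. The Saturday window follows the Thursday session and covers 48 h to 71 h.
- The first 24 h after the three weekly sessions make 3 × 24 = 72 h. With 60-minute sessions, 0 h of these are recorded. With the 70 minutes given in Exercise Training Protocol, two windows overlap by 10 minutes each, or 0.33 h. If the 5-minute transition is added (75 minutes), the overlap is 2 × 15 minutes = 0.5 h.

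In a training week, roughly the first day after each session is therefore missed, while later intake between sessions is recorded.

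**2. When the recalls are taken**

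Evidence for recording during the intervention:
- The recall timetable follows the training timetable on all three days, to the hour.
- Covariate variable (dietary assessment) speaks of tracking and monitoring intake, and Rationale & background information of strict dietary monitoring.
- Problems anticipated treats dietary variability as a difficulty of implementation and names the covariate as the statistical control for it.
- Study design lists anthropometric, cardiovascular and biochemical measures as the pre and post assessments. Diet is not among them, and no baseline recall is described elsewhere.

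Evidence that leaves it open:
- No study week or visit is given, and the same weekday windows could be used in a week before randomisation.
- Data management and statistical analysis justifies the covariate by variability in nutritional habits, which would fit a habitual or baseline value.

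**3. Size if the covariate is post-randomisation**

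Let *a* be the arm's effect on recorded intake (SD) and *b* the change in outcome per SD of intake. In a linear model without unmeasured common causes of intake and outcome, total effect = direct effect + *a* × *b*, so adjustment moves the estimate by *a* × *b*. All inputs are assumptions. So is the total effect of −0.5 SD used as a yardstick, because the Protocol says only that effects are moderate.

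| *a* | *b* | *a* × *b* | Share of −0.5 SD |
| --- | --- | --- | --- |
| 0 | 0.1 to 0.5 | 0 | 0% |
| −0.2 | 0.1 to 0.5 | −0.02 to −0.10 | 4% to 20% removed |
| −0.5 | 0.1 to 0.5 | −0.05 to −0.25 | 10% to 50% removed |
| +0.2 | 0.1 to 0.5 | +0.02 to +0.10 | 4% to 20% added |

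For example, −0.5 × 0.3 = −0.15 and −0.15 / −0.5 = 30%. If the covariate is taken before randomisation, *a* is zero by design.

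**The case against.** The strongest objection is that the Protocol never says diet is recorded after randomisation. A reader might take it as stated, because the windows track the sessions so closely. It is an inference: if the recalls belong to a baseline week, the bias is zero. This stands, and the point is conditional for that reason.

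It can also be said that the choice of diet value belongs in the SAP, which Project management assigns to the statistician and which is not at hand. That has some force for which value enters the model. It has less for when recalls are taken, which is a data-collection decision; an SAP cannot supply a baseline recall that was not collected.

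Four further readings are tempting but not supported:

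- *That intake after sessions is never recorded.* Only about the first 24 h are missed. The same clock times are given for everyone, so the gap mainly adds measurement error unless intake in those hours differs by arm. That is possible, because the missed day follows exercise in the training arms only, but it is a minor point.
- *That the dietary guidance itself drives the arms apart.* It is meant to keep diet stable and is not described as specific to an arm.
- *That the diet adjustment is the trial's main protection against bias.* Study design and Quality assurance also list randomisation, stratification, masked assessment and calibration, and nothing ranks diet first.
- *That a given share of the effect is lost.* Any percentage rests on assumed inputs, including a numerical effect size that the Protocol does not give. For the contrast between the two sequences, which use identical exercises, nothing in the document supports a large difference in intake.

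**Conclusion.** The point holds in conditional form. It is certain that diet is the only covariate named for the primary model, that each recall window ends at a session start, and that neither a study week nor a baseline recall is given. Recording during the intervention is the natural reading, but it is not stated.

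On that reading, the covariate may lie on the path from exercise to outcome, and the adjusted contrast does not estimate the total effect of the randomised regimen. The document fixes neither size nor direction. The distortion is zero if the arms do not shift intake, and 0.02 to 0.25 SD in absolute value over the assumed non-zero shifts and slopes. The change is worth making because it is cheap and removes the problem whichever reading was intended.

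**What to change.** In Covariate variable (dietary assessment) and in Data management and statistical analysis, state that the dietary covariate is mean energy intake from a three-day recall completed before randomisation. Report intake during the 12 weeks by arm, and use it only in an analysis labelled as sensitivity or mediation.

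Protocol Identifying Number says that the trial was registered during the intervention period, so a baseline recall may no longer be obtainable. If none exists, make the model without diet the primary one and the diet-adjusted model a sensitivity analysis.

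Recording some intake in the day after a session, with the same windows in all arms, would improve the description of in-trial diet. It is optional and does not affect the primary model once the covariate is a baseline value.

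The cost is a sentence in each of two sections and one extra set of recalls at baseline. The sample size stays at 39, and a baseline covariate uses the same single degree of freedom.
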